# **Design, Development and Randomized Control Trial of a Mobile Cessation intervention for Chinese adult smokers: Study Protocol**

## **Background**

### **Mobile health technology can promote smoking cessation and improve outcomes**

Many studies have confirmed that smart phone application (app) can promote smoking cessation and improve health outcomes. Apps based on behavior-change interventions include beneficial features of short messages and internet-based interventions, but without their specific limitations. App interventions can reach out to smokers proactively, unobtrusively with personalized and confidential messages that are cost effective. Support can be offered with or without internet connection, providing effective in-the-moment help, increasing smokers involvement and tracking progress at any time. Mobile based cessation programs are increasingly part of m-health programmes promoted and supported by WHO.

Up to now, dozens of mobile tools can be used as smoking cessation support for IOS and android systems. Some limitations, however, have been identified for smokers including that: not all tools follow international smoking cessation guidelines; the content and theory used in development process is not clear; researchers cannot take advantage of previous experiences; and most studies focus on short-term impact on smoking cessation rather than longer term evidence. Currently, there is neither high quality evidence to target Chinese population nor effective mobile cessation tools that could support patients to quit from smoking.

### **Primary objective**

We aim to develop a mobile cessation intervention based on Wechat app to support smokers to quit based on behavior-change intervention theories while taking into consideration of the context for Chinese people. After this, we will conduct a randomized controlled trial (RCT) to compare the efficacy of this tailored and behaviour change theory-based text message smoking cessation intervention with a nonpersonalized text message smoking cessation intervention.

### **Secondary objectives**

1. To evaluate potential impact on health awareness and self-efficacy for smokers between the two kinds of interventions.

2. To identify whether certain patients are more likely to benefit from these interventions.

## **Methods**

This study will be conducted in two steps. We firstly develop a smoking cessation intervention platform on Wechat based on TranstheoreticalModel (TTM) and Protection Motivation Theory (PMT). Both models have been independently applied to health behavior change interventions. After this, a prospective RCT using two-arm design will be conducted to assess the efficacy of this app-based treatment.

### **Step 1 Development of mobile cessation intervention**

The design and development of this mobile cessation intervention followed three main stages.

The first stage was to develop the conceptual and theoretical framework, which was based on the interactive application of Transtheoretical Model (TTM) and Protection Motivation Theory (PMT).

TTM posits that health behavior change can be divided as six stages: pre-contemplation, contemplation, preparation, action, maintenance, and termination. It is a systematic theory of behavior change that states that health behavior is determined on a stage-to-stage basis. For any specific stage, there is intervention method to strengthen the behavior change occurrence and/or support to achieve next stage. The premise for using this theory is readiness for change. People in action, maintenance or termination stage will be normally excluded in high quality RCT design due to the homogeneity requirement.

PMT provides an important social cognitive account of protective behavior and has been extended to a more general theory of persuasive communication. There are studies applying the model to predict and evaluate protective behavior, particularly health behaviors. Applied to smoking cessation intervention, PMT theory will be used to adjust smoking behaviors' threat and coping appraisal. Behavioral intervention will be conducted from the perspective of those quitting attempt inducing factors to

enhance smokers' perception of the severity and susceptibility of smoking related diseases. The theories underlying intervention design are further described in **Table 1**.

**Table 1. Conceptual and theoretical framework of Wechat application**

| Theory | Application                             | Description                                                                                                                                                                                                                                                                                                                                                                                                                                                                                                                                                                                         |
|---------------|------------------------------------------------|------------------------------------------------------------------------------------------------------------------------------------------------------------------------------------------------------------------------------------------------------------------------------------------------------------------------------------------------------------------------------------------------------------------------------------------------------------------------------------------------------------------------------------------------------------------------------------------------------------|
| TTM           | Actively identify smokers' stage               | Patients' willingness to quit will be assessed according to TTM. Smokers are divided as pre-contemplation, contemplation and preparation stage.                                                                                                                                                                                                                                                                                                                                                                                                                                                            |
| PMT           | Evaluate smokers' cessation protect motivation | Develop multitask interactive function to evaluate smoking behaviors' threat appraisal and coping appraisal, including perception of the severity and susceptibility of smoking related diseases, intrinsic and extrinsic rewards, and self-efficacy, etc.                                                                                                                                                                                                                                                                                                                                                 |
| PMT           | Strengthen cessation protect motivation        | Personalized interventions will be provided according to demographic characteristic (such as age, gender, education), social psychological factors (such as personality, social status), structural factors (such as perception of smoking and disease) and take into consideration current smokers' cessation protect motivation level.                                                                                                                                                                                                                                                                   |
| TTM           | Provide stage-to-stage continuous support      | Provide stage-to-stage support based on the systematic relationship between stages of change and processes of change. Consciousness rising, dramatic relief, environmental reevaluation strategies will be used to support smokers to reach contemplation stage; Self-reevaluation strategy will be used to support smokers to reach preparation stage; Self-liberation strategy will be used to support smokers to reach action stage; Helping relationships, Counterconditioning, Reinforcement management, and Stimulate control strategies will be used to support smokers to reach maintenance stage. |

In the second stage, we will hold several meetings. Experts in smoking cessation, health education, and IT will join the meetings and will provide comments and suggestions for the content. Then, the study team will revise those sections accordingly.

The last stage is to develop the mobile cessation tool on Wechat platform by using IT technology. We will take into account several important considerations. First, the app should ensure confidentiality of the data provided by the smokers. Second, the

system needs to be user friendly with ease for quick data entry. Third, there needs to be a back-end server that stores the data for future analysis. Fourth, it should be usable and adaptable for common operating systems. Finally, the information must be presented in a way that is easily read and interpreted. Therefore, Lime JS, an HTML5 framework for touch screens and desktop browsers, will be chosen as the basis for the development of this App. A single code base will be used for two different versions of the App: iPad and iPhone. MySQL database will be used for keeping track of the smoker's data and behavior in the App. On the server port, with multi-tier architecture, this app is divided into display layer, business layer and data layer to improve system reliability. In addition, in view of the possible high concurrent requests, container technology is used to implement the rapid deployment strategy of multi-service instances, and a streaming media player server is established for video and audio playback to ensure fast response under the condition of high concurrent requests.

## **Step 2 Prospective RCT of Wechat-based intervention for smoking cessation**

### **Enrolment procedures and eligibility criteria**

Smokers will be invited to participate in this study if they fulfill the following criteria:

- (1) Daily or weekly smokers
- (2) aged 18 or older
- (3) owned a mobile phone and used WeChat
- (4) Agree to participate and sign informed consent form.

Patients will be excluded from the study if:

- (1) Received any smoking cessation treatment within 30 days
- (2) With HIV/AIDS or any mental diseases
- (3) With other severe diseases that cannot follow doctor's advice
- (4) Unwilling to participate or unable to finish the study.

### **Ethical consideration and informed consent**

The trial was approved by the Ethics Committee of Peking University Health Science Center (IRB00001052-30063) Informed consent will be signed by all

recruited patients in their first visit.

### **Randomization**

An independent statistician, [name] [name] from Guanghua School of Management, Peking University, will oversee the randomization but will not be involved in the treatment. After recruitment, participants were required to complete the baseline questionnaire and register through WeChat. With a randomized block design and the score of the Fagerström Test for Nicotine Dependence as a stratified factor, eligible participants were assigned to the intervention group or the control group. The WeChat system was also used to balance demographic characteristics. Randomization was fully computerized and automated with equal allocation. The researchers and participants were all blinded.

### **Baseline assessment**

Research staff will conduct a face-to-face interview with recruited smokers in their first visit for baseline assessment. The interview will take approximately 15-30 minutes to complete and answers will be recorded directly into a computerized database. After completing the entire baseline assessment, participants will be given gift.

### **Interventions**

All the participants were informed that the 8th day after randomization would be their quit day. Participants who were allocated to the intervention group received tailored and behaviour change theory-based text message smoking cessation intervention. Control group participants received a nonpersonalized text message smoking cessation intervention developed by the National Cancer Institute (NCI). It was based on well-established cognitive-behavioural cessation approaches. The details of the control group can be found elsewhere. Both groups received information by Wechat and received 1-2 messages a day for 3 months after randomization.

A Standard Protocol Item: Recommendation for Interventional Trials (SPIRIT) is presented in Table 2.

### **Table 2. Standard Protocol Item: Recommendation for Interventional Trials**

|                           |          | Follow-up (month) |   |   |   |
|---------------------------|----------|-------------------|---|---|---|
|                           | Baseline | 1                 | 2 | 3 | 6 |
| ENROLMENT                 |          |                   |   |   |   |
| Eligibility screen        | X        |                   |   |   |   |
| Informed consent          | X        |                   |   |   |   |
| Allocation                | X        |                   |   |   |   |
| INTERVENTIONS             |          |                   |   |   |   |
| Intervention group        |          | X                 | X | X |   |
| Control group             |          | X                 | X | X |   |
| ASSESSMENT                |          |                   |   |   |   |
| Smoking status            | X        | X                 | X | X | X |
| Nicotine dependence       | X        | X                 |   | X | X |
| Willingness to quit       | X        | X                 | X | X | X |
| Prolonged abstinence      |          | X                 | X | X | X |
| Health awareness          | X        | X                 | X | X | X |
| Self-efficacy             | X        | X                 | X | X | X |
| Utilization of the Wechat | X        | X                 |   | X | X |

### Follow-up visit arrangement

All participants are instructed to attend face-to-face interview with research staff 1-month, 3-month, 6-month after randomization.

At each follow-up visit, the participants will be assessed smoking status. We will also test expired air carbon monoxide at all follow-up visits.

### Primary and Secondary outcome

The primary outcome was the biochemically verified 6 month sustained abstinence rate, defined as the self-report of no smoking any cigarettes after the designated quit date, validated biochemically by an expired carbon monoxide level of less than 6 ppm at each follow-up point.

Secondary outcomes are comprised of two aspects:

1. biochemically verified sustained abstinence rate at 1 month, 3 months, 1-3 months and 3-6 months, biochemically verified 24-hour point prevalence of abstinence at each follow-up point, self-reported sustained abstinence rate and 24-hour point prevalence of abstinence at each follow-up point

2. the change in nicotine dependence measured by the Fagerstrom Test for Nicotine Dependence, the change in nicotine withdrawal symptoms measured by the Minnesota Nicotine Withdrawal Scale, and the change in the readings of expired carbon monoxide.

3. Smoking cessation related health behavior: stage of change, self-efficacy, threat appraisal, coping appraisal and protection motivation.

4. Utilization of the app: time application opened, time of utilization, function used and self-report preference.

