### **Statistical analysis**

Descriptive statistics will be conducted to compare the baseline status between the two groups.

Data will be analyzed on an intention-to-treat (ITT) basis. In accordance with the ITT principle, all patients will be included in the analysis, independently of the groups to which they are randomly assigned and regardless of whether they complete the treatment or not. Participants who breach the protocol (taking cessation medication or received other cessation treatment) will be followed-up in their original group and classified according to their smoking status consistent with other participants.

The Russell Standard (RS) will be used in this study. All randomized subjects will be included in the denominator for calculating abstinence rates with the exception of unavoidable loss to follow-up (died or moved to an untraceable address). Those who decline to be involved in subsequent data collection will be counted as smokers. This type of analysis is considered the most conservative and is the standard for smoking cessation studies.

The primary and secondary abstinence outcomes will be analyzed by logistic regression of smoking status at each timepoint. The dependent variable is smoking

status (still smoking=0, abstinent=1). The independent variable is each intervention versus the control condition. Odds ratios (Or) will be used to measure the outcomes for the intervention groups compared to the control group, and 95% confidence intervals (CI) and P values will be reported to infer efficacy. In sensitivity analyses, each model will be further adjusted for baseline covariates: living area, age, education, smoking frequency and nicotine dependence at baseline.

All data will be analyzed using SPSS version 21.0. The level of bilateral significance for all statistical tests will be established at  $\alpha = 0.05$ .

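### The secondary 24-hour point-prevalence outcomes count some unchanged weekly smokers as abstinent, which inflates the rates in both arms and pulls the odds ratio towards 1

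*Protocol*

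**What the plan says.** Protocol, Enrolment procedures and eligibility criteria: the first inclusion criterion is "Daily or weekly smokers". Weekly is not defined in days per week.

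Protocol, Primary and Secondary outcome: the secondary outcomes include "biochemically verified 24-hour point prevalence of abstinence at each follow-up point" and "self-reported sustained abstinence rate and 24-hour point prevalence of abstinence at each follow-up point". No longer window is set for people who do not smoke every day. The primary outcome is of another kind. It is sustained abstinence, "defined as the self-report of no smoking any cigarettes after the designated quit date", and is "validated biochemically by an expired carbon monoxide level of less than 6 ppm at each follow-up point". The 6 ppm cut-off appears only there.

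Protocol, Follow-up visit arrangement: participants attend a "face-to-face interview with research staff 1-month, 3-month, 6-month after randomization", with expired CO measured each time.

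Protocol, Statistical analysis: "The primary and secondary abstinence outcomes will be analyzed by logistic regression of smoking status at each timepoint". The sensitivity analyses adjust for "living area, age, education, smoking frequency and nicotine dependence at baseline". Under Randomization, the stratification factor is the Fagerström score, not daily versus weekly smoking.

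**The concern.** A 24-hour question asks only about the last day. For a daily smoker, a smoke-free day is a change from usual behaviour. For someone who smokes on one or two days a week, it is the usual state, and that person could have met the criterion at baseline. The two provisions therefore do not fit together: for part of the eligible population, the measure does not separate quitting from no change.

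Randomisation should spread these participants evenly, so the expected result is a similar number of false abstainers in each arm. The reported point-prevalence rates would be too high and the treatment contrast too small on the odds-ratio scale. These outcomes are to be reported at every follow-up with odds ratios, confidence intervals and P values as evidence of efficacy, so a diluted estimate could be misread as a weak effect.

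**Working it through.** **The plan's own figure.** The only computed figure is the sample size, for 4% versus 10% continuous abstinence at 6 months. The unpooled formula gives (1.960 + 0.842)² × (0.04×0.96 + 0.10×0.90) / 0.06² = 280 per group, as stated. The total is 560 × 1.2 = 672, or 336 per arm. This calculation does not use the 24-hour outcome. Only the 336 is carried forward.

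**Step 1: one unchanged participant.** If the visit day falls at random relative to smoking days, a person who smokes on k days a week reports a smoke-free preceding day with probability (7−k)/7.

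| k (days a week) | 1 | 2 | 3 | 4 | 5 | 6 |
|---|---|---|---|---|---|---|
| Counted abstinent at a visit | 86% | 71% | 57% | 43% | 29% | 14% |

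This is the self-reported version. The verified version gives the same result only if CO is below 6 ppm at that visit.

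**Step 2: the whole arm.** Let w be the share of weekly smokers (assumed; not in the protocol) and p the true rate. The background is b = w(7−k)/7 and the observed rate is p + (1−p)b. This takes true quitting to be equally likely in daily and weekly smokers.

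Illustrative true rates are 10% and 18% (assumed; the protocol gives no planning rates for point prevalence). Power is for a two-sided 5% test with n = 336 per arm, by the pooled two-proportion formula: Φ{[d√n − 1.96√(2p̄(1−p̄))] / √(c(1−c) + t(1−t))}, where c and t are the observed rates, d = t − c and p̄ is their mean.

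Example, w = 10%, k = 1: b = 0.10 × 6/7 = 0.086; c = 0.10 + 0.90 × 0.0857 = 0.177; t = 0.18 + 0.82 × 0.0857 = 0.250; odds ratio 1.55; power 64%.

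| w | k | b | Control | Intervention | Odds ratio | Power |
|---|---|---|---|---|---|---|
| 0 | – | 0 | 10.0% | 18.0% | 1.98 | 85% |
| 2% | 2 | 1.4% | 11.3% | 19.2% | 1.86 | 81% |
| 5% | 3 | 2.9% | 12.6% | 20.3% | 1.78 | 78% |
| 5% | 1 | 4.3% | 13.9% | 21.5% | 1.70 | 74% |
| 10% | 5 | 2.9% | 12.6% | 20.3% | 1.78 | 78% |
| 10% | 3 | 5.7% | 15.1% | 22.7% | 1.64 | 71% |
| 10% | 1 | 8.6% | 17.7% | 25.0% | 1.55 | 64% |
| 20% | 3 | 11.4% | 20.3% | 27.4% | 1.48 | 58% |
| 20% | 1 | 17.1% | 25.4% | 32.1% | 1.38 | 48% |

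**Step 3: missing participants.** Only people who attend can be falsely abstinent. If 20% are missing and counted as smokers, the 8.6% background falls to 0.8 × 8.6% = 6.9%. At w = 10% and k = 1 to 2, the odds ratio is then about 1.60 to 1.64 and power 68 to 71%, somewhat less diluted.

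**Step 4: is it corrected elsewhere?** Adjusting for smoking frequency in a sensitivity analysis changes the comparison of groups. It does not reclassify a continuing smoker recorded as abstinent. Counting those who decline follow-up as smokers affects only people who do not attend.

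**The case against.** The strongest reply is that the main result is safe. A weekly smoker who continues and reports truthfully fails the primary definition, and the sustained-abstinence secondary outcomes do not use the 24-hour window either. The sample size rests on sustained abstinence, and the protocol plans no power for point prevalence. The bias runs towards no effect, so it does not create a false benefit. All of this stands, and it limits the weight of the point.

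The size is also open. The weekly share, the days per week and the 10% and 18% rates are all assumed, and small shares or more frequent smoking give little dilution. That stands too.

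Some stronger readings are tempting, but the documents do not support them:

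- A reader might infer that weekly smokers pass at most visits. That holds for 1 to 3 smoking days a week, not for 4 to 6, and the protocol does not say which weekly means.
- A reader might infer that the outcome fails to measure quitting for everyone. For daily smokers, a smoke-free day is a real, if possibly brief, change.
- A reader might infer that anyone who skips the day before a visit counts as abstinent. In the verified version CO must also be below the cut-off, and the protocol has no data on how often it would be.
- A reader might set the background against the planned 4% and 10%. Those are 6-month continuous rates, not point-prevalence rates.

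**Conclusion.** The point holds for the secondary point-prevalence outcomes, verified and self-reported, and only for those. The mechanism follows directly from the eligibility criterion and the outcome definition, and nothing in the protocol corrects it. The direction is clear: higher rates in both arms and an odds ratio closer to 1.

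The size is not settled. Under the stated assumptions it runs from slight (1.98 to 1.86 at a 2% share smoking 2 days a week) to large (1.98 to 1.38 at a 20% share smoking once a week). It rests on visit days unrelated to smoking days, truthful reporting, similar weekly shares in both arms and, for the verified version, CO below 6 ppm after a smoke-free day.

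This should be fixed because the improvement is cheap. A reader might infer that it threatens the trial's main conclusion; the primary definition rules that out.

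**What to change.** Define point prevalence as no smoking at all in the previous 7 days, with expired CO below 6 ppm for the verified version, and state that cut-off with the outcome. A participant who smokes at least one day in every 7 and says so can then no longer qualify. Keep the 24-hour measure only as a supplement, reported separately for daily and weekly smokers.

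The cost is one added question in interviews already scheduled, plus a change of wording. The downsides are lower headline rates and less comparability with 24-hour rates reported elsewhere; keeping the 24-hour measure as a supplement largely covers the second.
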